### Statistics

Currently at the UHN, approximately 20% of patients are readmitted to the hospital within 30 days post SOT. In general, these patients are readmitted following presentation to either the ambulatory transplant clinic or ED. Although we do not have data on the number of patients that present to the ambulatory transplant clinic within 30 days post SOT, previous work has shown ED visits at 30 days to vary greatly between SOT groups (eg, as low as 17% for patients with kidney transplants, and as high as 44% for patients with liver transplants) [24,25]. Given this variability, we hypothesized a conservative estimate of 20% for our 30-day composite end point. To observe a 50% relative risk reduction, from 20% to 10%, for the 30-day composite end point, at an alpha of .05 and power of 0.8, 199 participants will need to be recruited for each group.

We will evaluate all outcomes using the intention-to-treat analytical approach. A Cox proportional hazard model will be used to evaluate the effect of the mHealth app on posttransplant unplanned readmission and ED and unscheduled transplant clinic visit rates (primary outcome). Results of this analysis will be reported as hazard ratios with 95% CIs. Kaplan-Meier curves will be used to depict freedom from unplanned readmission. Subsequent to running the Cox proportional hazard model, a logistic regression model will be used to analyze unplanned readmission rates at the prespecified time points of 30 days, 3 months, and 1 year. Results of the logistic regression model will be reported using odds ratios and 95% CIs.

Generalized linear models to estimate the mean difference in the intervention compared to the control group will be used to estimate the impact of personalized communication through the mHealth app on posttransplant patient-reported outcomes (secondary outcomes).

To avoid spuriously inflated estimates of treatment effect, an interim analysis will be conducted when 50% of participants are enrolled and have completed follow-up. The results of this analysis will be reviewed by an independent data monitoring committee. The O’Brien-Fleming stopping rule will be used based on our primary outcome and requires a *P*≤.007 [26]. This conservative rule will avoid premature trial termination unless a large treatment effect is observed.

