## Introduction

Solid organ transplant (SOT) is the standard therapy for select patients with severe end organ dysfunction. During the transition from pre- to posttransplant, recipients are introduced to a number of new medications and medical issues. In light of this complexity, early hospital readmission is common, ranging from 18% to 47% [1-3]. In addition to an increased burden on the health care system, early hospital readmission is associated with increased patient morbidity and mortality [4]. Although some readmissions are unpredictable and unavoidable, as many as half of early readmissions may be preventable [4].

Mobile health (mHealth) technologies such as smartphones and wearable devices hold promise to reduce hospitalization and improve patient outcomes through real-time monitoring, prompting timely clinician intervention that cannot be replicated in traditional outpatient care [5]. A recent systematic review showed mHealth apps improve patient self-management and reduce rates of rehospitalization in adults with cardiovascular disease [6]. Previous work from our group has shown that mHealth technology is safe, feasible, and associated with a 50% relative risk reduction in rehospitalization in adults with heart failure [7]. We anticipate that SOT recipients would also benefit from improved monitoring and removal of communication barriers as the most common reasons for readmission (eg, infection, rejection, elevated blood pressure, and metabolic derangements such as renal, glucose, and electrolyte abnormalities) and mortality may be mitigated by clinical intervention [1,2,5,8]. Additionally, medication adherence is critical in transplant patients to prevent graft rejection [9,10]. Enhanced and clear communication is likely to lead to improved patient outcomes.

Over the past decade, the number of SOTs in Canada has increased by 33% [11]. As transplant program volumes continue to grow, the need to reduce hospital readmissions is critical both for patients and to avoid straining the health care system. Building upon prior research in which the safety and feasibility of mHealth technologies in adult patients with heart transplants was demonstrated [12], larger scale clinical data is needed to determine whether this technology reduces hospital readmissions.

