### Outcomes

The primary outcome for this study will be any unscheduled hospital admission or ED and unscheduled transplant clinic visit post discharge from the index admission during which the patients received their organ transplant. Readmissions and unscheduled ED/transplant clinic visits will be captured at 30 days, 3 months, and 1 year after organ transplant. A Central Adjudication Committee (CAC) composed of two transplant physicians from each organ group (ie, heart, kidney, and liver) will review each reported readmission to determine if they are study events and the most responsible diagnosis for readmission. Secondary outcomes will be assessed to capture participant illness experience and further quantify between-group differences in recovery from index transplantation. These will include patient-reported outcomes using validated self-administered questionnaires (see next section), 1-year graft survival rate, 1-year patient survival rate, number of Easy Call interactions, and index length of stay compared to pretransplant activity level (ie, step count). The CAC will also review all reported secondary outcomes and cases of graft loss or patient death to adjudicate the cause. Any disagreements within the CAC will be resolved by consensus.

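### Death is outside the primary composite, so the planned Kaplan-Meier curves overstate the proportion readmitted, and the logistic analyses slightly favour an arm with more early deaths

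*Protocol article*

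**What the plan says.** The Outcomes section of the protocol article defines the primary outcome as "any unscheduled hospital admission or ED and unscheduled transplant clinic visit post discharge from the index admission". Death and graft loss are not components. They appear among the secondary outcomes as "1-year graft survival rate, 1-year patient survival rate", and the adjudication committee reviews "cases of graft loss or patient death to adjudicate the cause". Nothing links a death to the primary outcome.

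The Statistics section fixes three methods, all by intention to treat:

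- For the primary outcome: "A Cox proportional hazard model will be used to evaluate the effect of the mHealth app".
- For display: "Kaplan-Meier curves will be used to depict freedom from unplanned readmission".
- As a follow-up to the Cox analysis: "a logistic regression model will be used to analyze unplanned readmission rates at the prespecified time points of 30 days, 3 months, and 1 year".

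The article does not mention competing risks, cumulative incidence, censoring at death, or the coding of a patient who dies without an event.

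**The concern.** A patient who has died can no longer be readmitted, so death competes with the outcome. Kaplan-Meier has only two states for a patient who leaves the risk set: event or censored. With death not an event, it is censored, and the curve then describes a hypothetical population in which nobody dies first. One minus that curve is not the proportion of patients actually readmitted. A logistic model by intention to treat records whether a readmission occurred by the time point, so a patient who died on day 20 without one is a non-event, the most favourable value.

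Two statements in the article make it hard to treat death as ignorable. The Introduction says that "early hospital readmission is associated with increased patient morbidity and mortality", so patients who die are probably not a random sample with respect to readmission risk. The Discussion says the trial will show whether the app improves patient and graft survival, so the investigators themselves allow that mortality may differ by arm. If it does, the logistic comparison moves towards the arm with more deaths, and a reader of the published curves cannot recover the true proportions readmitted.

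**Working it through.** **1. The plan's own figure.** Inputs from Statistics: 20% versus 10% at 30 days, alpha .05 (taken as two-sided), power 0.8. With the pooled-variance formula,

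n = [1.960·√(2·0.15·0.85) + 0.8416·√(0.20·0.80 + 0.10·0.90)]² / 0.10² = (0.9897 + 0.4208)² / 0.01 = 199 per group.

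This matches the article and does not depend on the present point.

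**2. How far one minus Kaplan-Meier exceeds the proportion readmitted.** The article gives neither a 1-year readmission rate nor a mortality rate, so both are assumptions: 50% readmitted within a year, and 1%, 3% or 5% dying first. Let h and d be constant cause-specific hazards of readmission and of death. Then

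- proportion readmitted = h/(h+d) · [1 − exp(−(h+d))]
- proportion dying first = d/(h+d) · [1 − exp(−(h+d))]
- one minus Kaplan-Meier, with death censored = 1 − exp(−h).

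The first two give h + d = −ln(1 − 0.50 − died first) and h = (h+d) · 0.50/(0.50 + died first).

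| Died first | h + d | h | 1 − Kaplan-Meier | True proportion | Non-events by death, per 200 |
|---|---|---|---|---|---|
| 1% | 0.713 | 0.699 | 50.3% | 50% | 2 |
| 3% | 0.755 | 0.712 | 50.9% | 50% | 6 |
| 5% | 0.799 | 0.726 | 51.6% | 50% | 10 |

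**3. Effect of an imbalance in deaths on the 1-year logistic comparison.** Give both arms the same readmission hazard (no treatment effect), and let 1% die first in one arm and 4% in the other. The readmission risk with death censored is set at 40%, 50% or 60%.

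| Risk with death censored | Readmitted, 1% arm | Readmitted, 4% arm | Shift | Odds ratio (4% arm vs 1% arm) |
|---|---|---|---|---|
| 40% | 39.8% | 39.1% | 0.7 points | 0.97 |
| 50% | 49.7% | 48.8% | 0.9 points | 0.96 |
| 60% | 59.6% | 58.4% | 1.2 points | 0.95 |

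The shift is smaller than 3 points because a death removes a readmission only if that patient would otherwise have been readmitted.

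If death were instead counted as an event, the 50% row would read 49.7 + 1 = 50.7% against 48.8 + 4 = 52.8%, a difference of 2.1 points in the opposite direction. The two codings therefore differ by 0.9 + 2.1 = 3 points. That is the only sense in which a 3-point imbalance is worth 3 points.

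**4. The 30-day time point.** Take 20% and 10% as the risks with death censored, and assume a 30-day death risk of 0.5-5%, equal in both arms. The proportions readmitted are then 19.95% and 9.98% at the low end, and 19.5% and 9.75% at the high end. About 0.9 to 9 patients per 199 die first.

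**5. What adding death to the composite would cost.** In the same 30-day model, if the intervention does not affect death, power at 199 per group falls to 0.774 with 1% mortality and 0.672 with 5%. Restoring 80% power would need 213 and 270 per group.

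**The case against.** The strongest reply is that only a condensed article is shown. Censoring rules, the coding of deaths at fixed time points and supportive competing-risk analyses commonly sit in a statistical analysis plan. This stands in part. A reader might infer that the plan itself prescribes censoring deaths or scoring them as successes. It does not: that treatment is a consequence of the named methods, and an analysis plan could add to them. But the composite, the Kaplan-Meier display and the logistic time points are stated choices, and they are what this point addresses.

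Other parts of the reply also stand:

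- The endpoint is broad. Where the full composite is analysed, only deaths after index discharge with no prior admission, emergency visit or unscheduled clinic visit matter. If nearly all deaths follow a counted event, the effect is smaller still.
- Deaths are not hidden. Patient survival is reported separately and causes are adjudicated.
- The direction is not always in the intervention's favour. If the app improves survival, more of its patients remain at risk of readmission, and the logistic analyses lean against it.
- A reader might infer that the primary Cox analysis is invalid. It is not. With death censored it estimates a cause-specific hazard ratio, which is a legitimate quantity, although it does not by itself translate into a difference in the proportion readmitted.

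**Conclusion.** The point holds at modest size. The named Kaplan-Meier display does not estimate the proportion readmitted. The logistic models, as specified, let a death before any event count as a good outcome.

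On the assumed 50% readmission and 1-5% dying first, the 1-year curve is too high by about 0.3-1.6 points, and 2-10 patients per 200 are non-events because they died. A 3-point imbalance in such deaths moves the 1-year readmission difference by about 0.7-1.2 points towards the arm with more deaths. It would be wrong to call this a 3-point bias in readmission: that figure applies only relative to an endpoint that counts death.

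At 30 days, the time point used for sizing, the effect is negligible unless early mortality is high. The 199 per group is unaffected, and no stated figure is wrong. All sizes rest on constant hazards and on rates that the article does not supply. Larger or more unbalanced mortality would enlarge them.

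**What to change.** - Replace the Kaplan-Meier plot with Aalen-Johansen cumulative incidence curves by arm, with death as a competing event.
- Report the Cox result as a cause-specific hazard ratio.
- Add a supportive analysis in which death counts as an event, once for the Cox model and once for each of the three logistic time points, and state how deaths are coded in the main logistic models.
- Keep the composite and the sample size. Moving death into the primary endpoint would lose power if the app does not affect mortality (step 5 of the working), so the death-as-event analyses should remain supportive.

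The cost is four supportive models and a changed plot, using survival data that the trial already collects. Fixing this before unblinding avoids an argument after the fact if deaths prove unbalanced. Label: cheap improvement.

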## Methods

### Overview

Remote Mobile Outpatient Monitoring in Transplant (Reboot) 2.0 is a registered (ClinicalTrials.gov NCT04721288) two-phased single-center study. It has also been approved by the University Health Network (UHN) Research Ethics Board (REB 20-6082.0.1). The first phase will consist of a 1-year concealed randomized controlled trial of 400 adult SOT (heart, kidney, or liver) recipients. Currently, the Ajmera Transplant Centre at the UHN (a large academic teaching site in Toronto, Canada) uses paper medical administration records to alter immunosuppressive medications, and patients generally record their vitals by pen and paper, both of which may be error prone. Additionally, health care providers and patients with transplants rely on a telephone-based (“Easy Call”) method of communication, wherein patients leave a message for their health provider when issues arise. The integration of medication and vitals tracking, as well as patient-provider communication into a single mHealth app may decrease errors and improve patient outcomes. To test this, participants will be randomized to receive either personalized communication using an mHealth app in addition to the Easy Call system (intervention group) or Easy Call standard of care (control group; see Figure 1). In the second phase of Reboot 2.0, the data set from the 400 patients with SOTs collected as part of phase one will be evaluated in an attempt to identify early markers of rejection, infection, and graft dysfunction posttransplant.

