### Randomization

Concealment of allocation will be ensured by the use of a centralized 24-hour internet-based computerized randomization system. Participant will be the unit of randomization, and to protect against imbalance in known prognostic factors between groups, stratified randomization will be used. Stratification will be based on age (ie, 18-31 years, 31-50 years, or >50 years of age), organ transplanted (ie, heart, kidney, or liver), listing status (ie, urgent transplant or nonurgent transplant), and history of organ replacement therapy (ie, left ventricular assist device or dialysis). Block randomization, using four blocks, will ensure balance between participants randomized to the intervention and control groups.

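### The interim threshold of P≤.007 is not the O'Brien-Fleming boundary for one look at 50%: it is looser than the rule the protocol names, and no final level is paired with it

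*Protocol article*

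**What the plan says.** All the inputs are in the Statistics section of the protocol article. The trial is sized on the 30-day composite: "To observe a 50% relative risk reduction, from 20% to 10%, for the 30-day composite end point", and "at an alpha of .05 and power of 0.8, 199 participants will need to be recruited for each group". The Overview plans 400 participants in total.

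There is a single interim look: "an interim analysis will be conducted when 50% of participants are enrolled and have completed follow-up". The boundary is introduced as an O'Brien-Fleming rule: "Fleming stopping rule will be used based on our primary outcome and requires a *P*≤.007 [26". The section calls the rule conservative and says that it guards against stopping early without a large effect.

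The primary analysis is a Cox model, reported as hazard ratios with 95% confidence intervals. No significance level is given for the final analysis. The article does not say whether the interim Cox model uses only the half who have completed follow-up or everyone enrolled by then.

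**The concern.** A named group-sequential rule, the number and timing of looks, and the overall alpha together fix the interim boundary. Here all of these are given, and the printed threshold does not follow from them. The threshold is the operative number, because it is what the data monitoring committee would hold the interim P-value against.

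The mismatch, at 50% information, is in the liberal direction. A looser threshold makes stopping at half the participants more likely than under the named rule. An early stop would leave fewer patients for the 1-year graft and patient survival outcomes and for the phase-two dataset. It also works against the section's own stated aim of avoiding inflated effect estimates. And anyone who later attaches a standard O'Brien-Fleming final level to .007 would exceed 5% overall.

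**Working it through.** **Inputs.** Alpha .05, power 0.8, event proportions 20% and 10%, 199 per group, one look at 50%, interim threshold .007 (all from Statistics). Assumptions: 1:1 allocation, inferred from equal group sizes, and information fraction t = 0.5, equal to the participant fraction.

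**1. Sidedness, from the plan's own sample size.** With pooled variance and no continuity correction,

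n = [z(1−α/2)·√(2·0.15·0.85) + z(0.8)·√(0.2·0.8 + 0.1·0.9)]² / 0.10²

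= [1.960·√0.255 + 0.8416·√0.25]² / 0.01 = 198.96, so 199 per group.

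The stated figure is reproduced. The one-sided version gives 157, so alpha is two-sided .05.

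**2. The O'Brien-Fleming boundary at 50%.** Let Z1 and Z2 be the interim and final statistics. Under the null they are bivariate normal with correlation √0.5.

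- *Classical.* Bounds are C/√t at the interim and C at the end. Solving P(|Z1| ≥ C√2 or |Z2| ≥ C) = .05 gives C = 1.9774. Interim Z = 1.9774 × 1.4142 = 2.797, P = .0052. Final P = .0480.
- *Lan-DeMets O'Brien-Fleming-type spending.* Alpha spent at t = 0.5 is 4[1 − Φ(z(1 − .05/4)/√0.5)] = .00305. Interim Z = 2.963, P = .0031. Final Z = 1.969, P = .0490.
- *As printed.* P = .007 corresponds to Z = 2.697, below both.

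**3. Other readings of .007.**

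| Reading | Result |
|---|---|
| One-sided P, alpha .025, one look at 50% | .0026 |
| One-sided P, alpha .05, one look at 50% | .0088 |
| Information at which classical two-sided P = .007 | about 0.54 |
| Information at which Lan-DeMets spending = .007 | about 0.59 |
| One-sided P at the second of three equal looks | .0071 |

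Neither one-sided reading at 50% gives .007. The last three rows are designs that the article does not describe.

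**4. Chance of stopping at the interim under the design effect.** The design drift is 1.960 + 0.8416 = 2.8016. At t = 0.5 the mean of Z1 is 2.8016 × √0.5 = 1.981. P(stop) = 1 − Φ(c − 1.981):

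| Interim P | c | P(stop) |
|---|---|---|
| .007 | 2.697 | 23.7% |
| .0052 | 2.794 | 20.8% |
| .0031 | 2.958 | 16.4% |

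Here c is the two-sided normal quantile of the rounded P, so it differs slightly from the unrounded bounds in step 2.

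**5. Overall type I error with .007 at the interim**, by final level (same bivariate normal):

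| Final level | Overall error |
|---|---|
| .05 | 5.29% |
| .049 | 5.19% |
| .048 | 5.10% |
| .0470 | 5.00% |

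For comparison, the correct classical .0052 followed by .05 gives 5.20%. Most of the excess in the first row therefore comes from an unadjusted final level, and about 0.1 point from .007 itself.

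**6. Power.** With the interim look included, holding 80% power needs 199.7 per group (Lan-DeMets), 200.5 (classical) or 201.4 (.007 with .0470), against 199 stated and 200 planned. With 199 per group and .007/.0470, power is 79.5%.

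**The case against.** **Information may not be 50%.** This is the strongest point. Enrolment is expected from mid-2021 and data collection to finish by late 2023. With one year of follow-up, enrolment would last roughly 1.5 years. If accrual is uniform, everyone is already enrolled when half have completed a year. A Cox analysis of all data then available would hold more than half the events: about 0.80 to 0.92 of them, assuming accrual over 1.25 to 1.75 years and constant hazards of 0.5 to 2 per year. At those fractions .007 is stricter than O'Brien-Fleming, and .007 followed by .05 gives about 5.0% to 5.05%. So the claim that .007 stops too readily depends on analysing only the completed half. The point stands as a limit on direction and size. It does not rescue the number: .007 fits only about 0.54 to 0.59 information, which is neither 50% nor this range.

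**The source of .007 cannot be seen.** The article cites a reference that is not available here. But the rule, timing and alpha are all printed, and they do not produce .007.

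**A reader might infer that the 5% error rate is not held, and that sizing at .05 contributes to this.** The document does not support either step. It states no final level, and that level is commonly left to an analysis plan or monitoring charter, so its absence is not a fault in itself. An overall alpha of .05 is the correct input for sizing a group-sequential trial. Sizing affects power, not type I error.

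**The threshold is still demanding.** True, and calling it conservative is not false in a general sense. It is nevertheless less conservative, at 50% information, than the rule it is said to be.

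**Conclusion.** Wrong as written. For one look at 50% information with two-sided alpha .05, O'Brien-Fleming gives .0052 or .0031, and the article prints .007. At that information the printed value raises the chance of an interim stop under the design effect by about 3 percentage points over the classical rule (23.7% against 20.8%) and about 7 over Lan-DeMets (against 16.4%).

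The effect on type I error is conditional and small: up to about 0.3 points if the final test is at .05, about 0.1 if at .048, and none if at .0470. No loss of error control is established by the article itself. The sample size of 199 per group is sound apart from a power cost of at most about half a point.

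The size and direction rest on t = 0.5. If the interim Cox model takes in partial follow-up from all enrolled participants, the direction could reverse, but a fixed .007 would still not be the named boundary.

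**What to change.** Choose one of the following and state it in the protocol and the monitoring charter before any unblinded interim data are seen:

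- Name the O'Brien-Fleming version and print its pair of levels. At 50% information these are P≤.0052 at the interim and P≤.048 at the end (classical), or P≤.0031 and P≤.049 (Lan-DeMets).
- Keep P≤.007, drop the O'Brien-Fleming label, and test at .0470 at the end.

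Also state whether the interim Cox analysis uses only the participants who have completed follow-up or everyone enrolled. If everyone, do not print a fixed interim P. Specify the spending function and compute the boundary from the observed fraction of planned primary events.

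The cost is wording in two documents and at most about half a point of power. No extra patients are needed.

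### The interim threshold of P≤.007 is looser than the O'Brien-Fleming rule it is attributed to: one look at 50% information with two-sided alpha .05 requires P≤.0052

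*Protocol article*

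**What the plan says.** All the relevant text is in the Statistics section of the protocol article.

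- **Timing:** "an interim analysis will be conducted when 50% of participants are enrolled and have completed follow-up". This is the only interim look mentioned. An independent data monitoring committee reviews the result.
- **Rule and threshold:** the O'Brien-Fleming "stopping rule will be used based on our primary outcome and requires a *P*≤.007". The article calls the rule conservative and supports it with a citation.
- **Design error rate:** the sample size is set "at an alpha of .05 and power of 0.8", with the conclusion that "199 participants will need to be recruited for each group". Sidedness is not stated.
- **Primary analysis:** a Cox proportional hazards model. "Results of this analysis will be reported as hazard ratios with 95% CIs".
- **Final significance level:** none is printed. The .05 appears only as the design alpha in the sample size statement.

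**The concern.** An O'Brien-Fleming boundary is fixed by three things: the overall alpha and its sidedness, the number of looks, and the information fraction at each look. The article gives or implies all three, so the threshold can be checked, and .007 is not the value they produce. It errs on the permissive side, although the article presents the rule as a guard against stopping too soon.

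Two things are at stake. First, a committee that applies the named rule and one that applies the printed number would decide differently for any interim P between .0052 and .007. That should be settled before unblinded data are seen. Second, a looser interim threshold spends more alpha at the first look. Unless the final level is lowered to match, the overall 5% is not held.

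**Working it through.** **Inputs (Statistics section)**
- Overall alpha .05, power 0.80, event proportions 20% and 10% at 30 days, 199 per group.
- One interim look at 50% of participants, information fraction taken as t = 0.5.
- Interim threshold P≤.007.
- No futility rule is described, and none is assumed.

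**Step 1. Is the design two-sided?** Reproduce the sample size with the pooled-variance formula:

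n = [z_α √(2·p̄(1−p̄)) + z_β √(p₁(1−p₁) + p₂(1−p₂))]² / (p₁−p₂)², with p̄ = 0.15.

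- Two-sided: [1.960·√0.255 + 0.842·√0.25]² / 0.01 = 198.96, so 199 per group. This is the article's figure.
- One-sided: replacing 1.960 by 1.645 gives 156.6, so 157 per group.

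Only the two-sided test returns 199, and the 95% confidence intervals fit it. I take alpha .05 as two-sided.

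**Step 2. The boundary for the stated design.** Under the null hypothesis, the interim and final statistics (Z₁, Z₂) are bivariate normal with correlation √0.5. The classical O'Brien-Fleming rule sets c₁ = C/√t and c₂ = C, with C solving

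Pr(|Z₁| ≥ C/√0.5 or |Z₂| ≥ C) = .05.

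Numerical integration gives C = 1.977:
- interim z = 1.977/√0.5 = 2.797, two-sided P = .0052
- final z = 1.977, two-sided P = .0480

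The Lan-DeMets O'Brien-Fleming-type function, applied to each side at .025, spends 4[1 − Φ(2.241/√0.5)] = .0031 at t = 0.5:
- interim z = 2.963, P = .0031
- final z = 1.969, P = .0490

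**Step 3. Does any other standard reading at the half-way look give .007?**

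| Reading | P at the half-way look |
|---|---|
| Classical, two-sided .05 | .0052 |
| Lan-DeMets type, two-sided .05 | .0031 |
| Classical, one-sided .05 | .0088 |
| Lan-DeMets type, one-sided .05 | .0056 |
| Classical, one-sided .025 | .0026 |
| Four-look classical, second look, two-sided .05 | .0042 |

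None does. Two-sided, .007 (z = 2.697) is the classical boundary at t ≈ 0.54 and the Lan-DeMets type at t ≈ 0.59. The middle look of a three-look design has a two-sided P of .0141 (one-sided .0071), but it falls at 67% information and is not the planned design.

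**Step 4. Overall two-sided type I error at t = 0.5**

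α = 1 − Pr(|Z₁| < c₁ and |Z₂| < c₂)

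| Interim P | Final P | Overall α |
|---|---|---|
| .007 | .050 | 5.29% |
| .007 | .049 | 5.19% |
| .007 | .048 | 5.10% |
| .007 | .047 | 5.00% |
| .0052 | .050 | 5.20% |

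The last row separates the two sources of excess. With a final .05, an interim .0052 already gives 5.20%, so the looser interim threshold adds only 5.29 − 5.20 = 0.09 percentage points.

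**The case against.** **The information fraction need not be 0.5.** The primary test is a Cox model, so information accrues with events. The look is triggered when half the participants have completed follow-up, which lasts one year (Study Follow-up section). Later enrolees may have had events by then. If their data are included, the fraction exceeds 0.5. The classical boundary is .0101 at t = 0.60 and .0164 at t = 0.70, so .007 would then be stricter than the named rule. With a final .05 the overall error would fall to 5.21% at t = 0.60, 5.12% at 0.70 and 5.05% at 0.80. This stands as a caution about direction. It does not justify the printed number: the article ties one fixed P to a 50% look and gives no other fraction. It does favour a boundary computed at the observed fraction.

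**The final level is not stated.** A reader might infer that the trial's type I error exceeds 5%, because .05 is the only alpha printed. The article does not support that. Its .05 is the overall design alpha from which a group-sequential plan starts, and naming O'Brien-Fleming implies an adjusted final boundary. Nor is the absence of the final level an error in itself: a condensed article may leave it to the full protocol or the SAP. What remains is that neither usual final level, .048 or .049, restores 5% when paired with .007 at half the information.

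**The excess is small.** This is correct: at most 0.29 percentage points, most of it from the assumed final .05.

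**The figure carries a citation.** The source is not available here, so how .007 was obtained is unknown. A citation does not change what the stated design requires.

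**The reason given for the look.** A reader might also make much of "To avoid spuriously inflated estimates of treatment effect, an interim analysis will be conducted when 50% of participants are enrolled". Stopping early on a significant result tends to exaggerate an effect, so the sentence is badly phrased. But the paragraph goes on to describe a strict threshold meant to prevent premature stopping, so the intention is recoverable. This is a matter of wording and adds nothing to the numerical point.

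**Conclusion.** P≤.007 is not the O'Brien-Fleming boundary for one look at 50% information with a two-sided alpha of .05. The classical value is .0052 and the Lan-DeMets type is .0031, so the printed threshold is looser than either version of the named rule.

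The consequence for type I error is conditional. At half the information, overall error is 5.10% to 5.29% if the final level is .048, .049 or .05, and is held at 5% only by a final level of about .047 or lower. The conclusion assumes two-sided testing (supported by the 199 per group), an information fraction of 0.5 and no futility rule.

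The point should be fixed because it concerns a decision threshold on the primary outcome and the correction is easy. The size of the error does not put the trial's validity in doubt.

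**What to change.** Choose one of the following and put the same figures in the protocol and in whatever document guides the data monitoring committee:

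1. **Classical O'Brien-Fleming at 50% information:** interim P≤.005, final P≤.048.
2. **Lan-DeMets O'Brien-Fleming-type spending function** at the observed event-information fraction. This suits the Cox analysis best, because the fraction may differ from 0.5. At exactly 0.5 it gives .0031 and .0490. The plan should then say whether participants still in follow-up contribute to the interim analysis.
3. **Keep .007** with a final level of about .047, and do not call the pair O'Brien-Fleming at 50%.

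Whichever is chosen, state that the tests are two-sided. It would also help to reword the reason for the look as early stopping for a large benefit.

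The cost is a few figures and a sentence. Under option 1 the interim critical z rises from 2.697 to about 2.80, and the final one is 1.977, against 1.960 for an unadjusted .05 test. Option 3 leaves the interim threshold alone and raises the final critical z to 1.986.
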